### 6.2.5.2 Analysis unit

The statistical unit for this analysis will be the cervical HPV infection for which it is assessed that a following histopathologically-confirmed CIN2+ (or CIN1+, or CIN3+) associated with the same HPV type is detected.

### 6.2.5.3 Event variable

The analyzed event - histopathologically-confirmed CIN2+ (or CIN1+, or CIN3+) associated with the same HPV type as the cervical HPV infection - will be analyzed by means of a binary variable with the following categories:

- 1 = Detection of a histopathologically-confirmed CIN2+ (or CIN1+, or CIN3+) associated with the same HPV type as the cervical HPV infection
- 0 = No detection of a histopathologically-confirmed CIN2+ (or CIN1+, or CIN3+) associated with the same HPV type as the cervical HPV infection or no detection of a histopathologically-confirmed CIN2+ (or CIN1+, or CIN3+)

In case more than one histopathologically-confirmed CIN2+ (or CIN1+, or CIN3+) associated with a cervical HPV infection are detected, only the first CIN2+ (or CIN1+, or CIN3+) in chronological order will be taken into account, whether the histopathologically-confirmed CIN2+ (or CIN1+, or CIN3+) is detected prior, i.e. within the 12 months preceding the cervical HPV infection or after this infection.

The event will be determined as showed with the following examples (See section 8.4.2 for more details):

| Sub-
ject | Detected cervical HPV infections* and/or lesions
over the follow-up period                                                                                                                                           | Subject
included in
analysis
population | Event
(0 = No /
1 = Yes) |
|----------------------|---------------------------------------------------------------------------------------------------------------------------------------------------------------------------------------------------------------------------------|------------------------------------------------------------|-----------------------------------------|
| A                    | -                                                                                                                                                                                                                               | No                                                         |                                         |
| B                    | Transient infection associated with HPV type X
CIN associated with HPV type X                                                                                                                                                | Yes                                                        | 1                                       |
| C                    | 12-month persistent infection associated with HPV type X
CIN associated with HPV type X                                                                                                                                      | Yes                                                        | 1                                       |
| D                    | Transient infection associated with HPV type X
Transient infection associated with HPV type Y
6-month persistent infection associated with HPV type Z
CIN associated with HPV type X
CIN associated with HPV type Z | Yes                                                        | 1

1                              |
| E                    | 6-month persistent infection associated with HPV type X                                                                                                                                                                         | Yes                                                        | 0                                       |
| F                    | 6-month persistent infection associated with HPV type X
6-month persistent infection associated with HPV type Y
CIN associated with HPV type X                                                                            | Yes                                                        | 1
0                                  |

| Sub-
ject | Detected cervical HPV infections* and/or lesions
over the follow-up period | Subject
included in
analysis
population | Event
(0 = No /
1 = Yes) |
|--------------|-------------------------------------------------------------------------------|--------------------------------------------------|--------------------------------|
| G            | 6-month persistent infection associated with HPV type X**                     | Yes                                              | 0                              |
|              | 6-month persistent infection associated with HPV type X                       |                                                  | 1                              |
|              | CIN associated with HPV type X                                                |                                                  |                                |

\* Cervical HPV infections of same HPV type are separated by a clearance.

\*\* In case several cervical HPV infections (separated by a clearance), associated with the same HPV type, are detected for a same subject, the following rules will apply:

- the event will be associated primarily with persistent 6-month cervical infections, then with persistent cervical infections which durations are less than 150 days, then with transient infections and then with other infections.
- if several cervical HPV infections of the same kind are detected for the association with the event, the event will be associated with the immediate preceding (in chronological order) detected infection if a CIN2+ (or CIN1+, or CIN3+) associated with this HPV type is detected after this infection but before the following detected infections of same type.

(See Section 4.3.1 and flowchart in Section 8.2 for the definition and determination of incident, transient, persistent and other cervical HPV infections ; See Sections 4.3.2 to 4.3.4 for the definition of histopathologically-confirmed CIN2+ (or CIN1+, or CIN3+) associated with a given HPV type ; See Section 8.3.2 for the flowchart of data associated with this objective).

#### 6.2.5.4 Time computation

The time between the onset of a cervical HPV infection (any HPV infection) and a histopathologically-confirmed CIN2+ (or CIN1+, or CIN3+) associated with the same HPV type will be calculated in days as: Date of event or Date of censoring - Date of detection of the cervical HPV infection.

The date of event will be:

- the date of the detection of the histopathologically-confirmed CIN2+ (or CIN1+, or CIN3+) associated with the same HPV type as the HPV type of the cervical HPV infection,

The date of censoring will be:

- the date of Month 48 visit for subjects who attended all visits during the 48-month follow-up period and who had a histopathologically-confirmed CIN2+ (or CIN1+, or CIN3+) not associated with the same HPV type as the cervical HPV infection or who did not have a histopathologically-confirmed CIN2+ (or CIN1+, or CIN3+) or during this period,
- the date of the last PCR reported at the latest visit for which data are available or the date of the last cytology or the date of the last biopsy (if the date is after the date of the last PCR) for subjects who did not attend all visits during the 48-month follow-up period and who had a histopathologically-confirmed CIN2+ (or CIN1+, or CIN3+) not associated with the same HPV type as the cervical HPV infection or who did not have a

histopathologically-confirmed CIN2+ (or CIN1+, or CIN3+) throughout their follow-up period (from first to last visit).

- Special cases:
  - In case two distinct cervical HPV infections (i.e. separated by a clearance) associated with the same HPV type are detected for a same subject and a histopathologically-confirmed CIN2+ (or CIN1+, or CIN3+) associated with this HPV type is detected after the second infection, the date of censoring of the first infection will be the date of onset of the second infection since the event (i.e. detection of a histopathologically-confirmed CIN2+ (or CIN1+, or CIN3+)) is associated with the second detected infection (in chronological order).
  - In case a histopathologically-confirmed CIN2+ (or CIN1+, or CIN3+) associated with a given HPV type is detected before the detection of the first cervical infection of that HPV type, the time between the cervical infection and the histopathologically-confirmed CIN2+ (or CIN1+, or CIN3+) will be set to 0 (i.e. the date of the infection will be that of the histopathologically-confirmed CIN2+ (or CIN1+, or CIN3+)) if the delay between the histopathologically-confirmed CIN2+ (or CIN1+, or CIN3+) and the cervical HPV infection is less than 12 months (if the delay is more than 12 months, the event is censored).

These cases are illustrated in the following tables. The associations between the histopathologically-confirmed CIN2+ (or CIN1+, or CIN3+) and confirmed 6-month persistent cervical infections are showed in bold.

| Whatever the order of the cervical HPV infections                                                                      | a           | b                              | c                                   | d                     | e                 |
|-------------------------------------------------------------------------------------------------------------------------------|-------------|--------------------------------|-------------------------------------|-----------------------|-------------------|
| -                                                                                                                             | No CINx     | HPVx persistent 6 month        | HPVx persistent < 6 month           | HPVx transient        | HPVx other        |
| b-a ≤ 12 mo
c-a ≤ 12 mo or c-a > 12 mo or no c
d-a ≤ 12 mo or d-a > 12 mo or no d
e-a ≤ 12 mo or e-a > 12 mo or no e | CINx | HPVx persistent 6 month | HPVx persistent < 6 month           | HPVx transient        | HPVx other        |
| b-a > 12 mo or no b
c-a ≤ 12 mo
d-a ≤ 12 mo or d-a > 12 mo or no d
e-a ≤ 12 mo or e-a > 12 mo or no e                | CINx | HPVx persistent 6 month        | HPVx persistent < 6 month | HPVx transient        | HPVx other        |
| b-a > 12 mo or no b
c-a > 12 mo or no c
d-a ≤ 12 mo
e-a ≤ 12 mo or e-a > 12 mo or no e                               | CINx | HPVx persistent 6 month        | HPVx persistent < 6 month           | HPVx transient | HPVx other        |
| b-a > 12 mo or no b
c-a > 12 mo or no c
d-a > 12 mo or no d
e-a ≤ 12 mo                                              | CINx | HPVx persistent 6 month        | HPVx persistent < 6 month           | HPVx transient        | HPVx other |
| b-a > 12 mo or no b
c-a > 12 mo or no c
d-a > 12 mo or no d
e-a > 12 mo or no e                                      | CINx        | HPVx persistent 6 month        | HPVx persistent < 6 month           | HPVx transient        | HPVx other        |

| Whatever the order of the cervical HPV infections | b                                          | c                                                   | d                             | e                         | a               |
|----------------------------------------------------------|---------------------------------------------------|------------------------------------------------------------|--------------------------------------|----------------------------------|------------------------|
|                                                          | HPV x
persistent
6 month         | HPV x
persistent
< 6 month                | HPV x
transient        | HPV x
other        | No CIN x    |
| b
c or no c
d or no d
e or no e                 | HPVx
persistent
6 month | HPV x
persistent
< 6 month                | HPV x
transient        | HPV x
other        | CINx |
| no b
c
d or no d
e or no e                      | HPV x
persistent
6 month         | HPVx
persistent
< 6
month | HPV x
transient        | HPV x
other        | CINx |
| no b
no c
d
e or no e                           | HPV x
persistent
6 month         | HPV x
persistent
< 6 month                | HPVx
transient | HPV x
other        | CINx |
| no b
no c
no d
e                                | HPV x
persistent
6 month         | HPV x
persistent
< 6 month                | HPV x
transient        | HPVx
other | CINx |

### 6.2.5.5 Statistical methods

The time between any cervical HPV infections and lesions will be analyzed using the same models and methodology as for the analysis of the time between persistent cervical HPV infections and lesions (cf. Section 6.2.4.5).

## 6.2.6 Analysis of clearance of cervical HPV infections

### 6.2.6.1 Population

The population for the analysis of the clearance of a cervical HPV infection will be restricted to subjects from the TVC-1-Control arm cohort for whom at least one cervical HPV infection was detected over the follow-up period so that a clearance of absence of clearance can be assessed.

### 6.2.6.2 Analysis unit

The statistical unit for this analysis will be the cervical HPV infection for which the clearance is assessed.

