## **6 STATISTICAL ANALYSES**

### **6.1 Statistical considerations**

#### **6.1.1 General considerations**

All analyses/summaries will be performed using either SAS version 9.1 or higher. They will be done on all 14 countries of the study pooled together.

Categorical variables will be summarized by the frequency and the percentage of each category. The following statistics will be presented for continuous variables: number of non-missing observations, mean, standard deviation, median and range (minimum and maximum).

Unless specified otherwise, two-sided 95% confidence intervals for percentages will be computed using an exact method based on the binomial distribution (Clopper-Pearson method [Newcombe, 1998]).

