## **6.2.3 Description of endpoints and determinants**

### **6.2.3.1 Endpoints and clinical determinants**

Endpoint and clinical determinants defined in Section 4.3 and in Section 4.4.2 will be summarized over the 48-month follow-up period for the TVC-1-Control arm cohort.

When relevant, endpoint density estimates will be calculated by dividing the number of incident events (i.e. progression to lesion, first cervical HPV infection) by the length of follow-up in person months of subjects at risk.

The description of endpoints will additionally be presented stratified according to clinical or behavioral determinants of interest, such as HPV type.

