#### **6.2.6.4 Statistical methods**

The clearance of cervical HPV infections (two definitions) will be analyzed using marginal binary-response models such as generalized estimating equation (GEE) regression models for clustered binary responses [Zeger et al., 1988].

These multivariable analyses will allow taking into account that women may contribute to several observations related to different HPV types, resulting in multiple event times, in addition to estimating the simultaneous effects of determinants. The GEE approach will adjust for the dependency caused by the repeated observations on the same subject by estimating robust standard errors for parameter estimates. The appropriate correlation matrix structure accounting for within-subject correlation will be determined at the time of the statistical analysis based on the patterns observed.

Interactions between determinants of interest and the type of cervical HPV infection will be explored by introducing interaction terms between these determinants and a variable categorizing the type of cervical HPV infections as transient or other, 6-month persistent and 12-month persistent (See Sections 4.4.2 and 4.4.3 for the definition of behavioral and clinical determinants and Section 8.5.2 for the list of determinants that will be taken into account in the analysis). In the presence of strong interactions, the analyses will be stratified according to the type of cervical HPV infection.

Results from the multivariable regression models will include odds ratios (95% CI).

Depending on the results, other models taking into account the time between cervical HPV infections and their clearance (i.e. Cox regression models) may be used also as described in Section 6.4.2.5. In such case, cervical HPV infection detected at the last visit will be excluded of the analysis because they will all be censored at day 0.

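### The default exact binomial interval has no exception for percentages of infections, so an interval on a per-infection clearance percentage would ignore within-woman dependence

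*SAP*

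**What the plan says.** SAP 6.1.1 sets the general rule for percentages: "Unless specified otherwise, two-sided 95% confidence intervals for percentages will be computed using an exact method based on the binomial distribution". It names the Clopper-Pearson method.

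For clearance, SAP 6.2.6.2 defines the unit: "The statistical unit for this analysis will be the cervical HPV infection for which the clearance is assessed". Section 6.2.6.3 codes each infection 0 or 1 under each of the two clearance definitions. Section 9.3.3 adds that every infection is counted.

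Section 6.2.6.4 recognises that "women may contribute to several observations related to different HPV types" and deals with it inside the model: "The GEE approach will adjust for the dependency caused by the repeated observations on the same subject by estimating robust standard errors for parameter estimates". For that model, odds ratios with 95% intervals are the listed output; a model-based clearance percentage is not listed.

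On description, 6.2.3.1 says that the endpoints defined in Section 4.3, which include clearance, "will be summarized over the 48-month follow-up period for the TVC-1-Control arm cohort". It then adds: "The description of endpoints will additionally be presented stratified according to clinical or behavioral determinants of interest, such as HPV type". It states neither the denominator nor an interval method for these summaries. No section writes an exception to 6.1.1 for percentages of infections.

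**The concern.** The binomial interval treats every unit in the denominator as independent. For percentages of women that is reasonable. For percentages of infections it conflicts with 6.2.6.4, which treats infections in the same woman as dependent. The plan therefore uses robust standard errors for the odds ratios but leaves its default for percentages on the assumption that it rejects there.

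The SAP itself gives reasons to expect the dependence to be positive:

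- Woman-level determinants are assigned to all of a woman's infections (6.1.2) and examined as predictors of clearance (9.5.2). Any real effect makes her infections alike in an unadjusted percentage.
- A type first detected at the last visit, or followed only by a missing last-visit result, is coded as not cleared (4.5.1, 9.2). A woman with two such types contributes two zeros together.
- Section 4.4.2 lists 25 types (14 high-risk and 11 low-risk), and a type may recur after clearance, so several infections per woman are expected.

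The secondary objective is to describe clearance as well as to evaluate its determinants. At stake is whether a 95% interval printed beside a pooled or woman-level clearance percentage has close to 95% coverage.

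**Working it through.** **Inputs.** From the SAP: the unit is the infection (6.2.6.2), a woman may have several (6.2.6.4), and the default is the exact binomial interval at 95% (6.1.1). The SAP gives no clearance percentage, number of infections, infections per woman or within-woman correlation, so there is no plan figure to reproduce. Everything below rests on assumed values.

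**Design effect.** With mean m infections per infected woman, coefficient of variation c and intraclass correlation r:

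DE = 1 + (m(1 + c²) − 1)r

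- m = 2.8, c = 0.8, r = 0.02: 1 + (2.8 × 1.64 − 1) × 0.02 = 1.07
- m = 2, c = 0.7, r = 0.1: 1 + (2 × 1.49 − 1) × 0.1 = 1.20
- m = 3, c = 1.0, r = 0.1: 1 + (3 × 2 − 1) × 0.1 = 1.50
- m = 4.1, c = 0.8, r = 0.12: 1 + (4.1 × 1.64 − 1) × 0.12 = 1.69, about 1.7

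**Width and coverage.** In the normal approximation the correct interval is √DE times the plain one. The plain one is therefore short by 1 − 1/√DE, and its coverage is 2Φ(1.96/√DE) − 1.

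| DE | Correct interval wider by | Plain interval too short by | Coverage |
|---|---|---|---|
| 1.07 | 3% | 3% | 94% |
| 1.20 | 10% | 9% | 92.7% |
| 1.50 | 22% | 18% | 89.0% |
| 1.70 | 30% | 23% | 87% |

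**Conservatism of the exact method.** Clopper-Pearson is slightly wider than nominal. At a clearance proportion of 0.7 this offsets a design effect of up to about 1.07 with 200 infections, 1.03 with 1000 and 1.015 with 5000. With two infections per woman (DE = 1 + r), that is a correlation of about 0.07, 0.03 and 0.015.

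**Simulation check.** Beta-binomial data, 2000 women, 1 to 6 infections each (mean 2.1), clearance 0.7, 4000 runs:

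| Correlation | DE | Clopper-Pearson coverage | Cluster-robust coverage |
|---|---|---|---|
| 0 | 1.00 | 95.1% | 94.7% |
| 0.05 | 1.10 | 94.4% | 95.4% |
| 0.1 | 1.20 | 93.0% | 94.6% |
| 0.2 | 1.39 | 90.0% | 94.7% |
| 0.3 | 1.59 | 88.4% | 94.6% |

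The exact interval is sound at zero correlation and loses coverage as correlation rises. The clustered interval holds throughout.

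**Absolute size.** With 1000 infections and 70% cleared, the exact interval is 67.05% to 72.83%, 5.8 points wide. At a design effect of 1.2 it should be about 6.3 points wide.

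**The case against.** The strongest reply is that the plan nowhere promises such an interval. Section 6.1.1 summarises categorical variables by frequency and percentage; its sentence on intervals fixes the method for those that are given and does not say that every percentage gets one. Section 6.2.3.1 names neither an interval nor a denominator. The only clearance interval named is for the odds ratios, and it is cluster-robust. This stands, and it is why the point is conditional. It does not remove the gap: if an analyst adds an interval to a per-infection percentage, the only written rule gives the wrong one.

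A reader might infer that the clearance analysis ignores clustering. It does not. The GEE handles it, and comparisons by region, smoking and other woman-level factors rest on the GEE odds ratios.

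A reader might also infer that the intervals are certain to be too narrow, or by a known amount. The documents do not support this. Narrowness needs positive within-woman correlation; the mechanisms listed make that plausible, but its size is not given. Nor is 30% the shortfall at a design effect of 1.7: the correct interval is 30% wider, so the plain one is 23% too short.

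Finally, the only stratifier named in 6.2.3.1 is HPV type. Within one type most women would be expected to contribute a single infection (an assumption, since types can recur), so those percentages are nearly unaffected.

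**Conclusion.** The point holds in a limited form. The default in 6.1.1, applied to a percentage of infections, assumes an independence that 6.2.6.4 rejects, and no exception is written. It matters only where a clearance percentage is shown per infection with an interval, pooled over types or by a woman-level determinant, and only if clearance is positively correlated within women.

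Under assumed design effects of 1.07 to 1.7, coverage falls from about 94% to 87%. At the lower end the conservatism of the exact method may cancel the effect, more so with few infections. The odds ratios and their intervals are unaffected. The impact is modest and descriptive, and no conclusion of the clearance analysis is shown to depend on it.

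**What to change.** In 6.1.1, add as a stated exception that Clopper-Pearson applies to percentages of subjects, and that any 95% interval for a percentage of infections is clustered on the woman.

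In 6.2.6.4, name the method: a logistic GEE with robust variance, intercept-only for an overall percentage or with one factor for a stratified one, with the limits transformed back to the percentage scale. The same section already uses this approach for the odds ratios. If no interval is intended for these percentages, saying so would also close the gap.

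The cost is one sentence in each section and a few lines of SAS, with no new data. The downside is somewhat wider descriptive intervals.
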